### Recruitment

All participants diagnosed with prostate cancer at the urology outpatient clinic who meet the eligibility criteria are invited to participate. These participants are identified by the research nurses from all participants with prostate cancer who are discussed at the multi-disciplinary team meeting (MDT) prior to being informed of their diagnosis. At the diagnosis appointment, a clinical nurse specialist introduces the research by saying “We are conducting lifestyle research within the department, are you willing for a research nurse to call you to discuss this further?” If the participant agrees, their contact details are passed on to the research nurse. An informational flyer is available.

The research nurses telephone the potential participants, explain the trial, answer any questions, and confirm eligibility. Eligible and interested participants are then emailed or posted a detailed information sheet. To ensure maximum recruitment, any participants who are missed at the diagnosis clinic are phoned by a member of the clinical care team to explain the trial and provide more information as above. For all participants, the research nurse phones again a few days later once the information has had time to arrive and be read. For those participants still wishing to participate, initial telephone consent is requested for randomisation and preparation of metformin prescriptions (if appropriate). A baseline face to face research appointment is scheduled for approximately 1 week before treatment is due to begin.

Recruitment of participants into the trial will continue until the target sample size of 122 (i.e. *n* = 54, active surveillance; *n* = 40, surgery; *n* = 28, external beam radiotherapy/brachytherapy) has been reached.

### Treatment arm specifics

The trial pathway differs slightly for those undergoing the different treatment pathways.

#### Radical prostatectomy

During radical prostatectomy, participants in the trial have tissue samples extracted and stored. Participants are asked to note how much activity they can do post-surgery and at what stage they feel they are back to their pre-surgery activity. Participants have an additional questionnaire 7 weeks following main consent (approximately 6 weeks after surgery).

#### Active surveillance

As well as being identified from the MDT, active surveillance patients are identified from the cancer register. These participants are contacted 5 to 6 months into the active surveillance pathway, re-screened and sent trial information. Participants on active surveillance undergo a second biopsy, as part of standard care, at 12 months following diagnosis and this recruitment delay allows biopsy data to be timed to be collected after 6 months follow-up.

#### External beam radiotherapy or brachytherapy

Participants undergoing external beam radiotherapy and brachytherapy follow the research pathway as per protocol, with an additional questionnaire at 4.5 months post main consent.

### Research clinic 1: baseline

At the initial research clinic appointment, informed consent is re-confirmed, and the consent form is signed. Baseline data are collected, based on all the outcome measures to be collected at follow-up. Participants are informed of their intervention group and provided with specific intervention group instructions.

The research nurse ensures that the participants know how to carry out their interventions. Participants in the metformin group are seen briefly by a urologist and provided with 3 months medication. All participants are provided with a pedometer to wear continuously for the 6 months duration of the trial. In addition, participants in the physical activity intervention are provided with a Garmin ‘Vivofit 4’ activity tracker to wear for the 6 months duration of the trial intervention. All participants will be given a 7 day monitoring form where they log their daily step count over 1 week and, where appropriate, whether they have completed 10,000 steps, achieved the target brisk walking and taken their metformin tablet. This monitoring form is returned to the trial team by post.

Following baseline research appointment, a letter is sent to the participants’ GP, informing them that their patient is participating in the research trial and letting them know which intervention group they are in.

Approximately 6 weeks after surgery, participants undergoing radical prostatectomy receive an additional urinary symptom questionnaire.

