### Interventions

#### Physical activity intervention

Participants allocated to the physical activity group are instructed to walk at a brisk pace for 30 min, on at least 5 days a week, on top of normal physical activity, with the additional aim to walk 10,000 steps every day. They are provided with a waist worn pedometer and a wrist worn Garmin ‘Vivofit 4’ activity monitor. Both the pedometer and Garmin activity monitor will be worn throughout the 6 months duration of the brisk walk intervention. The pedometers measure the number of steps and will be worn throughout the day. The Garmin monitors will be worn day and night and measure number of steps, minutes of moderate physical activity and sleep, and provide movement reminders when an individual has been sedentary for an hour. They can be set to celebrate personalised activity goals and data are available for the individual to view on a smart phone or desktop computer for live feedback. Participants will be asked to record their daily step count for 1 week at baseline, 3, 6, and 12 months follow-up. Physical activity intensity will be recorded by the Garmin activity monitor.

COVID-19 contingency: Participants allocated to brisk walk as part of their intervention will be offered the option of home-based exercises if they are unable, or feel uncomfortable with, brisk walking outside due to COVID-19. Participants will be informed of these exercises via a letter, which will include a 10-min steps workout routine to conduct indoors. This exercise routine is designed to be of similar intensity to brisk walking and safe to perform at home. Participants will be advised that these exercises can be repeated three times a day (30 min in total).

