### Analysis plan

The primary comparative analyses are by intention-to-treat for randomisation rates and adherence to treatment. Baseline characteristics for each group are tabulated using means and standard deviations for normally distributed data, medians and interquartile ranges for non-normally distributed data, and percentages and counts for categorical data. Outcome measures at baseline and follow-up are tabulated to assess the range of values to inform sample size calculations for a definitive trial. Secondary outcomes are tabulated as described above.

The measures made on the tissue and blood samples are research measures and do not have any direct clinical relevance for the participant or their routine clinic treatment. Analysis includes mean serum, plasma, and tissue levels of components of the IGF axis, including IGF-I as a biomarker of prostate cancer progression, and PSA level. Concentrations of IGF-I will be measured using gold standard ‘in-house’ radioimmunoassays. PSA levels will be measured using standard methods employed by the study’s NHS Pathology laboratory. Bloods and tissue may also be analysed for genetic, epigenetic, and metabolomic biomarkers.

Semi-structured face-to-face or telephone interviews will be conducted with participants to explore their experiences of their allocated intervention and the trial generally. Purposive sampling will be used to recruit up to 5 participants from each of the interventions, who underwent different treatment types and who wore the wearable activity tracker. The interviews will be audio-recorded, transcribed, anonymised, and analysed thematically using a qualitative method. A qualitative analysis computer program, such as NVivo [39], will be used to assist with the analysis.

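### The step count labelled 'baseline' is logged in the week after men learn their allocation, so in the two walking groups it is most likely not a pre-intervention value

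*Protocol article*

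**What the plan says.** The protocol article (Physical activity intervention) asks men to "record their daily step count for 1 week at baseline, 3, 6, and 12 months follow-up". Table 1 likewise places a pedometer step count at research clinic 1.

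The section on research clinic 1 describes how that first count is obtained:

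- Disclosure and instruction: "Participants are informed of their intervention group and provided with specific intervention group instructions".
- Tablets: "Participants in the metformin group are seen briefly by a urologist and provided with 3 months medication".
- Device: "All participants are provided with a pedometer to wear continuously for the 6 months duration of the trial". The walking groups also receive the Garmin monitor here.
- Recording: "All participants will be given a 7 day monitoring form where they log their daily step count over 1 week". Where applicable, the same form asks "whether they have completed 10,000 steps, achieved the target brisk walking and taken their metformin tablet".
- Return: "This monitoring form is returned to the trial team by post".

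The Analysis plan then states: "Outcome measures at baseline and follow-up are tabulated to assess the range of values to inform sample size calculations" for a definitive trial.

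**The concern.** A baseline value should describe a man before the intervention can have changed him. Here the pedometer is first issued at the visit where allocation is disclosed, and the week of logging follows. Participants are not blinded, so the count is taken in the knowledge of the group.

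This matters most in the walking groups. Their walking is prescribed in addition to each man's usual activity, so usual activity is the natural reference for judging what was added. If the recorded week already contains prescribed walking, a table headed 'baseline' mixes two quantities: roughly usual activity in the control and metformin-only groups, and usual activity plus early uptake in the walking groups. A difference between groups in that table could be read as chance imbalance when it is really early response. Anyone planning the definitive trial who took a baseline mean, a change SD or a baseline-to-follow-up correlation from those values would be working from the wrong quantity.

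**Working it through.** **Order of events.** No formula applies to this part; the check is whether any reading of the text gives a step count before disclosure.

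1. *Could the count precede the visit?* The pedometer is issued to all men at research clinic 1. No earlier device, posted pedometer or run-in week is described.
2. *Could it be taken at the visit?* The same section says that baseline data on all follow-up outcome measures are collected there. That can cover questionnaires, weight and blood. It cannot cover seven days of counts from a pedometer handed over that day.
3. *So it follows the visit.* Return by post agrees with this.
4. *Is that week on intervention?* No sentence gives the first day of walking. Three features point to the visit as the start:
   - The devices issued there are worn for the six-month intervention and returned at the six-month clinic.
   - Three months of tablets are supplied there and renewed at the three-month visit.
   - The form asks about the step target, the brisk walking and the tablet.

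   In the walking groups the Garmin, described under Strategies to improve adherence as a motivational tool, is also issued at this visit.
5. *Does this apply equally to all groups?* No. Controls are asked to keep to their normal activity, and metformin-only men receive no walking instruction.

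**Use of the value.**

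- Primary walking adherence is the one-week step count at six months, judged against a 50% rate. No baseline term is stated.
- The sample size of 122 (54 + 40 + 28) rests on the recruitment rate and does not involve step counts.
- The planned use is the baseline and follow-up tabulation in the Analysis plan.

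**Possible size.** The protocol gives no figure for this, so there is none to reproduce.

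- From the protocol: 30 minutes per walk, and the minimum of 5 walks a week.
- Assumed: 100–120 steps per minute. The documents give no cadence.
- Formula: extra steps/day = minutes × cadence × walks per week ÷ 7.

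| Share of the five walks done in week 1 | 100 steps/min | 120 steps/min |
|---|---|---|
| All | 30 × 100 × 5 ÷ 7 = 2,143 | 30 × 120 × 5 ÷ 7 = 2,571 |
| Half (illustration) | 2,143 ÷ 2 ≈ 1,071 | 2,571 ÷ 2 ≈ 1,286 |

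The daily 10,000-step aim is left out, because its effect depends on the unmeasured usual count. A man who did the same walking in week 1 and at month 6 would show no change from that source.

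**Room for an earlier log.** Table 1 places research clinic 1 about three weeks after allocation, which is long enough for a seven-day record before disclosure.

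**The case against.** The strongest reply is that nothing planned depends on this value. The primary outcome has no baseline term, no change score, change SD or correlation for steps is specified, and the protocol disclaims any test of efficacy. That stands. A reader might infer that the adherence result is invalidated or that a planned change analysis is biased; the document supports neither. The problem lies in what the label invites and in the table passed to the definitive trial.

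A reader might also infer that usual activity goes unmeasured by device in every group. That is too broad. Men without a walking instruction may well record something close to usual activity, subject to knowing their group and wearing a new pedometer. What is missing everywhere is a count taken before disclosure.

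The start day is indeed inferred. The form's adherence items apply only where relevant, and seven-day forms are used again at later visits, so the items alone do not prove that walking began at once. Together with device wear and tablet supply, the inference is reasonable but not certain.

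Baseline activity is also measured by the Godin questionnaire. This helps, but it is self-report and does not yield steps.

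Finally, an article condenses a fuller protocol. The point does not rest on an omission, however: the article sets out a specific procedure and gives the result a label that does not fit it.

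**Conclusion.** The point holds as one of labelling and interpretation. The 'baseline' step count is post-disclosure in all four groups. In the two walking groups it most likely reflects the first week on intervention, so it should not be presented there as a pre-intervention value or compared with the other groups as one.

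The figure of about 2,100–2,600 steps/day is what full adherence to five walks would add at the assumed cadence. It is not an expected bias: it would shrink in proportion to the walking actually done that week, and it does not apply to the control or metformin-only groups. The primary outcomes and the sample size are unaffected. Correction is still worthwhile because informing a definitive trial is this study's stated goal and the correction costs almost nothing.

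**What to change.** **This trial.** Recruitment finished on 16 March 2020, so the collection procedure can no longer be changed.

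- Label the record 'week 1 after allocation disclosure' in every table.
- Do not present it as baseline, and do not use it in any change score, SD or correlation passed to the definitive trial.
- Use the Godin questionnaire from research clinic 1 as the baseline activity measure. Confirm that it was completed before disclosure: the section mentions baseline data collection first, but does not say when in the visit each item was filled in.

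The cost is a change of table labels. The downside is reliance on self-report in place of a step count.

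**Definitive trial.** Issue the pedometer between telephone randomisation and research clinic 1, with a step-only seven-day form completed before allocation is disclosed. The telephone consent would need widening, since it currently covers randomisation and preparation of metformin prescriptions, and written consent comes only at the clinic. The cost is sending out the pedometers, one pre-visit task for participants and a change to the consent wording. A newly issued pedometer may itself alter behaviour, but it would do so before men know their group.

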### Research clinic 2: 3 months follow-up

Three months following main consent, and baseline appointment, the participants are sent the questionnaire again, along with a 7 day monitoring form, to be returned by post. The research nurse phones the participants to arrange the 3 months follow-up appointment. Participants will be given the option of performing their follow-up over the telephone, except for participants in the metformin groups who are asked to attend a face-to-face appointment. An additional blood sample is taken from the participants in the metformin groups and their suitability to continue taking metformin is reviewed, and a further 3 months metformin supply is provided.

Approximately 4.5 months post-randomisation, participants undergoing radiotherapy receive an additional symptoms questionnaire including a measure of cancer-related fatigue [36] and quality of life [35].

COVID-19 contingency: participants in the metformin group will have their follow-up appointment conducted over the telephone. Participants with a recent estimated glomerular filtration rate (eGFR) will be administered with a further 3 months supply of metformin either through collecting their metformin in person (with minimal social contact) at the trial site or via use of the hospital pharmacy courier service.

### Research clinic 3: 6 months follow-up

Six months after main consent, participants are sent the questionnaire and 7 day monitoring form to complete before the 6 months follow-up research clinic. At the research clinic, a blood sample is taken, pedometers and wrist worn activity monitors are returned and some participants will be invited to participate in a qualitative interview to explore experiences of the changes they were asked to make and of participating in the research overall.

To engage with the participants and maintain motivation throughout the 6 months intervention period, participants receive texts, emails, and posted materials.

COVID-19 contingency: all participants with have their follow-ups conducted over the telephone. Blood collection will be obtained up to and at 12 months follow-up. Participants will be advised to retain their pedometers for their 12 months follow-up and sent a prepaid envelope to those given a Garmin ‘Vivofit 4’ activity tracker to return the device. The research nurse approached participants about participating in an interview during their telephone follow-up. All interviews will be conducted over the telephone.

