**Assessments:**								
Demographic data			x		x		x	x
Family medical history			x		x		x	x
Height (cm)			x					
Weight (kg)			x		x		x	
Blood sample			x		(x)		x	
Leisure time physical activity [28]			x		x		x	x
Urinary symptoms [29]			x	x	x		x	x
Psychological factors [30, 31]			x		x		x	x
Patient function and bother [32]			x		x		x	x
Health beliefs [adapted from [33, 34]			x		x		x	x
Quality of life measures [35]			x		x		x	x
Cancer-related fatigue [36, 37]			x		x	x	x	x
Lifestyle behaviours (drinking and smoking)			x		x		x	x
Prostate tissue			[x]					
Step count (pedometer)			x		x		x	x
Physical activity intensity/step count (Garmin)			x		x		x	
Metformin tablet count			x		x		x	
Qualitative interview							x	

*RC* research clinic, *[x]* = collected during surgery 1-week post-baseline; *(x)* = metformin groups only

^a^Surgical participants only

^b^Radiotherapy participants only

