### 12 months follow-up

Questionnaire and 7 day monitoring data will be collected at 12 months follow-up via post, 6 months after the intervention has ended.

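### The standard procedure takes pedometers back at 6 months although a 12-month pedometer step week is scheduled; only the COVID-19 contingency lets participants keep them

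*Protocol article*

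**What the plan says.** **A step count at 12 months is scheduled.** The section on the physical activity intervention states: "Participants will be asked to record their daily step count for 1 week at baseline, 3, 6, and 12 months follow-up". Table 1 marks the pedometer step count at 12 months, while the separate row for the Garmin monitor ends at 6 months. The 12-month section adds: "Questionnaire and 7 day monitoring data will be collected at 12 months follow-up via post, 6 months after the intervention has ended". The baseline clinic section shows that this form holds the step log: "All participants will be given a 7 day monitoring form where they log their daily step count over 1 week".

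**The device is issued for 6 months and then collected.** The baseline clinic section gives every participant a pedometer for a 6-month wearing period. The 6-month clinic section then has it handed in: "At the research clinic, a blood sample is taken, pedometers and wrist worn activity monitors are returned".

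**The contingency differs.** Under the COVID-19 arrangements in that section, follow-up is by telephone and "Participants will be advised to retain their pedometers for their 12 months follow-up". Only the Garmin is posted back.

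**The concern.** A standing rule removes the instrument before a measurement that the schedule still requires. The reason given in the contingency for keeping the pedometer is the 12-month follow-up itself, so the article recognises that the device is needed then but provides for it only in the pandemic arrangements.

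At stake is the one device measure of walking after the intervention has ended. If it exists mostly for men who reached 6 months under the contingency, its availability depends on calendar time, and the tabulated 12-month values describe walking during the pandemic. The analysis plan uses tabulated follow-up values to inform sample size for a definitive trial. In a feasibility study, completeness of a measure is also a result in its own right. A gap created by collecting devices says nothing about whether men are willing to record steps at 12 months.

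**Working it through.** The article states no figure for 12-month step availability, so there is none to reproduce. The check has two parts.

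**1. Consistency of the text**

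| Place in the article | Pedometer at 6 months | Step count at 12 months |
|---|---|---|
| Physical activity intervention | worn for 6 months | required |
| Table 1 | count marked | count marked (Garmin row has ended) |
| Research clinic 1 | issued for 6 months | not addressed |
| Research clinic 3, standard | handed back | not addressed |
| Research clinic 3, contingency | kept | named as the reason for keeping it |
| 12 months follow-up | not addressed | form collected by post |

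No section describes retention, re-issue or posting of a pedometer outside the contingency.

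**2. Illustrative size**

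Inputs from the article:
- Recruitment ran from 11 September 2018 to 16 March 2020, which is 552 days, with 110 men recruited (Trial status).
- Remote delivery began in March 2020, and the amendment was approved in July 2020 (Methods).
- The 6-month contact is timed from main consent, which Table 1 places about 3 weeks after allocation.

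Assumptions: uniform accrual; 183 days from consent to the 6-month visit; a lag *L* of 0 or 21 days from recruitment to main consent; no withdrawals; and a single date *S* on which the advice to keep the pedometer begins. The article does not give *S*, so the first and last days used for March and July 2020 serve as a range.

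Share under the return rule = (days from 11 September 2018 to *S* − 183 − *L*) / 552.

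| *S* | *L* (days) | Share returning | Men returning | Men keeping |
|---|---|---|---|---|
| 1 March 2020 | 0 | 354/552 = 0.641 | 71 | 39 |
| 1 March 2020 | 21 | 333/552 = 0.603 | 66 | 44 |
| 16 March 2020 | 0 | 369/552 = 0.668 | 74 | 36 |
| 16 March 2020 | 21 | 348/552 = 0.630 | 69 | 41 |
| 1 July 2020 | 0 | 476/552 = 0.862 | 95 | 15 |
| 1 July 2020 | 21 | 455/552 = 0.824 | 91 | 19 |
| 31 July 2020 | 0 | 506/552 = 0.917 | 101 | 9 |
| 31 July 2020 | 21 | 485/552 = 0.879 | 97 | 13 |

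A March start leaves 36 to 44 men with a device, and a July start leaves 9 to 19. In every row more than half of the 110 men fall under the return rule. Men who keep the device reach 6 months in March 2020 or later, so their 12-month week falls from about September 2020 onward.

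**The case against.** Several points on the other side stand.

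- **The data are not shown to be unobtainable.** A reader might infer that 12-month steps can be collected only from men followed up under the contingency. The article does not go that far. It condenses a full protocol that is not shown, and it does not exclude posting a pedometer with the 12-month form or a man using his own device. What is established is that the stated procedure provides no trial device.
- **The counts are not a ceiling.** It is tempting to read the 36 to 41 men under a 16 March 2020 switch as a maximum. No accrual curve or start date for the advice is given. Slower early recruitment or late 6-month visits would raise the number, and a later start would lower it.
- **The main outcome is not touched.** The primary adherence measure is the 6-month pedometer week, and that form is completed before the 6-month clinic. The secondary outcome list names no 12-month step count; its 12-month activity measure is the Godin questionnaire, which needs no device.
- **Misreading the gaps as non-response is conjecture.** Nothing in the article says that missing 12-month steps will be classified that way.
- **No efficacy comparison is planned.** The dependence on calendar time therefore affects description and planning, not a treatment effect estimate.

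One reply does not stand: that this is only detail left to the full protocol. The article states the return rule outright, and that rule conflicts with the schedule it also states. Both appear as current text.

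**Conclusion.** The contradiction is real and moderate in weight. Followed as written, the standard 6-month procedure leaves men without the trial pedometer needed for a scheduled 12-month assessment, so post-intervention device counts would come mainly from men followed up during the pandemic.

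The number keeping a device runs from about 9 to 44 of 110, depending mostly on when the advice to keep it began. It rests on uniform accrual, exact visit timing and no withdrawals, and should be read as an order of magnitude. The textual conflict depends on none of these assumptions. The stronger readings, that no other man could supply a 12-month count or that the primary outcome is compromised, are not supported.

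**What to change.** Reconcile the baseline and 6-month clinic sections with the physical activity section, Table 1 and the 12-month section in one of two ways:

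1. State that all participants keep the pedometer until the 12-month form has been returned, or are posted one with the 12-month pack where that week is still to come.
2. Otherwise, remove the 12-month pedometer count from the schedule.

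In either case, report how many men had a device available at 12 months, give step completeness with those men as the denominator, and show it separately for the standard-return and contingency periods. Device collection is then not counted as participant non-response when the definitive trial is planned.

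The article expected data collection to finish on 31 March 2021. Keeping or posting devices therefore helps this trial only for weeks outstanding at the time of the change; after that, the reporting step and the lesson for the definitive trial remain. The cost is postage and pedometers out for 6 more months, with some risk of loss. The reporting step needs only a record of whether and when each device was returned.
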